## Abstract

**Introduction:**

Endovascular therapy is the main treatment for chronic limb-threatening ischaemia in the UK. Despite a restenosis risk of 50% over 2 years, reintervention rates are low, potentially resulting in preventable amputations. European guidelines recommend ultrasound surveillance to facilitate early treatment of restenosis. This study will investigate the use of duplex ultrasound after endo revascularisation (DUSTER). The aim is to assess the feasibility, acceptability and impact on clinical decision-making of a 1-year integrated ultrasound surveillance programme after lower limb endovascular therapy.

**Methods and analysis:**

DUSTER is a mixed-methods study. Phase I is a three-site, feasibility, open-label, randomised controlled trial. The standard of care, the control arm, is standard clinical surveillance by a vascular specialist at 1, 6 and 12 months. The intervention arm will receive integrated ultrasound (ankle-brachial pressure index, toe pressure and duplex) plus standard clinical surveillance. Primary outcomes are rates of attendance and completion of ultrasound surveillance tests, as well as the percentage of participants undergoing reintervention for restenosis. Secondary outcomes are limb salvage, amputation-free survival, reasons for amputation, complications, serious adverse events and mortality.

Phase II comprises independent semistructured interviews with intervention arm participants. The interviews will explore barriers and facilitators to ultrasound surveillance and the effect of ultrasound surveillance on patients’ lives.

Phase III has two separate focus groups for participants and clinical stakeholders to identify which outcomes matter most in any subsequent large-scale effectiveness trials.

**Ethics and dissemination:**

This research has been approved by a UK (West Midlands, Black Country) Research Ethics Committee (reference 24/WM/0232) and the Health Research Authority (IRAS 349192). Dissemination of results will be by the DUSTER co-investigators in peer-reviewed journals, to the National Institute for Health and Care Research and to a lay audience via the Mid and South Essex NHS Foundations Trust website.

**Trial registration number:**

NCT06702306.

STRENGTHS AND LIMITATIONS OF THIS STUDYThis is a multicentre study assessing uptake across three diverse geographic areas and patient populations, improving the generalisability of findings.The use of mixed methods will allow for a comprehensive understanding of feasibility through the collection of both quantitative outcomes and qualitative insights from participants.The study has been co-designed with the Limbless Association, a charity for the limb loss community, ensuring patient and public involvement.Feasibility and amputation endpoints are objective measures, not subject to bias.Due to the nature of the intervention, participant and clinician blinding is not possible.

## Introduction

 Approximately 4000 people in the UK undergo major lower limb amputation each year due to peripheral arterial disease.^1^ The end stage, chronic limb-threatening ischaemia (CLTI), is characterised by nocturnal foot pain, ulceration and gangrene. If untreated, CLTI progresses to amputation, sepsis and death. Hence, CLTI has been the focus of a UK initiative, which aims to reduce amputation rates by expediting limb salvage interventions.^2^ Amputation can have secondary psychosocial impacts, including social isolation, frustration, anxiety and depression.^3^ The average cost of a major amputation, including inpatient care, rehabilitation and prosthetics, is £15 000.^4^ Additionally, amputees may need to move house, require community care, home and vehicle adaptations or Personal Independence Payments and lose employment opportunities.

Endovascular therapy has become the primary modality of limb salvage in CLTI, with >17 000 procedures performed annually in the UK.^1^ These include angioplasty, stenting and advanced interventions, such as intravascular lithotripsy or drug delivery via balloons or stents. These procedures are successful in over 90% of cases, but over 2 years, half of the target vessels restenose or reocclude, putting limbs at risk again.^5^

A recent meta-analysis examined amputation rates following endovascular therapy.^6^ It revealed that 10% of patients lose their leg within the first year of treatment. Restenosis rates were reported at 33% after 1 year and 46% after 2 years. Despite this, reintervention rates were relatively low: 10% at 1 year and 25% at 2 years. This suggests potential for more reintervention to prevent amputations.

Currently, UK vascular specialists detect restenosis through worsening pain, non-healing wounds or loss of previously palpable foot pulses. Out of 51 UK specialists surveyed for duplex ultrasound after endo revascularisation (DUSTER), 83% used clinical follow-up alone. In contrast, the 2019 European Society for Vascular Surgery guidelines recommend three lower limb Doppler scans within the first year post-treatment, combined with ankle-brachial pressure index (ABPI) and toe pressure measurements, in addition to standard clinical follow-up.^7^

In the National Health Service (NHS), it remains unclear whether patients will attend additional scans, whether all scan components can be completed (given factors such as skin ulceration, oedema or toe amputation) or if these scans trigger treatment of restenosis. Ultrasound is safe, accurate and inexpensive. Every NHS vascular unit is equipped with ultrasound facilities, minimising barriers to implementation. Data from Mid and South Essex and Imperial College Healthcare NHS Trusts indicate high attendance rates for vascular ultrasound (95% in 2022–2023), suggesting that ultrasound surveillance should be feasible. If ultrasound prevented one in five amputations,^5^ it could result in NHS cost savings of £5–7 million per year. However, if ultrasound surveillance was introduced but was ineffective, it would increase sonographer workload, unnecessary reinterventions, complications and costs.

The DUSTER study aims to evaluate the feasibility, acceptability and impact of a 1-year integrated ultrasound surveillance programme for patients following endovascular therapy. It will pave the way for an effectiveness study to assess the clinical and cost-effectiveness of this approach, ensuring the surveillance strategy is streamlined and tested for wider adoption.

## Methods and analysis

### Trial design

DUSTER is a mixed-methods study comprising three phases. Eligibility criteria are shown in table 1.

**Table 1 T1:** Eligibility criteria

Inclusion criteria	Exclusion criteria
Adults (18 years or over) who have had successful lower limb endovascular therapy for chronic limb-threatening ischaemia*†‡	Surgical bypass or endarterectomy alone undertaken
Procedures within the last 3 weeks	Patient unfit for or does not want any future revascularisation
Interventions to iliac, femoral, tibial and pedal vessels alone or in combination	Need for major amputation due to gas gangrene, severe Charcot deformity, extensive tissue loss with unstable foot, severe pedal atherosclerosis on angiography or patient request
Able to give informed consent	Patient unwilling or cannot attend further surveillance
Endarterectomy or cutdown is permissible	Interventions for claudication or acute limb ischaemia or trauma
Participation in other vascular trials will be allowed if there is judged to be no risk of affecting validity of each trial by the chief investigators of DUSTER	Patients unable to take any form of antithrombotic therapy
	Prior leg endovascular therapy at the same anatomical location in the study leg (within 1 year)

* Chronic limb-threatening ischaemia refers to ischaemic rest pain, ulceration or gangrene with arterial imaging confirming peripheral arterial disease. Only one leg per patient is eligible for randomisation in DUSTER.

† Successful lower limb endovascular therapy is defined as <30% residual stenosis in the treated segments and patient leaving hospital without a major (above ankle) amputation on study leg.

‡ Endovascular procedures include angioplasty, stenting, atherectomy, lithotripsy, drug eluting balloon or stent or a combination.

DUSTER, duplex ultrasound after endo revascularisation.

Phase I is a multisite, randomised (1:1), controlled, open-label, two-arm feasibility trial. This trial will follow patients up for 13 months. Phase I is due to commence with recruitment in March 2025 and close with analysis in September 2026.

Phase II consists of independent semistructured interviews with intervention arm participants only, regarding their opinions of ultrasound surveillance. The interviews will be held as per participants’ preference on MS Teams or via telephone, after a minimum 6-month follow-up. The interviews will explore the individual’s quality of life, how they manage daily activities, how they look after their affected limbs, how they feel about surveillance and any impact it may have had on their disease/life and what barriers they experienced in completing ultrasound surveillance.

Phase III will include two separate focus groups of participants and clinical stakeholders to identify which of the outcome measures identified in phase I matter most in a follow-on effectiveness trial. This will help define secondary endpoints for a future trial and Health Technology Assessment application if specific progression criteria are met.

Please see figure 1 for a flow diagram of the study design and online supplemental appendix 1 for a Standard Protocol Items: Recommendations for Interventional Trials checklist.

**Figure 1 F1:**
[figure not shown]
DUSTER, duplex ultrasound after endo revascularisation; EQ-5D-L, European quality of life-five dimensions level; NRS-11, Numeric Rating Scale-11; QoL, quality of life; RCT, randomised controlled trial; VASCUQOL-6, Vascular Quality of Life Questionnaire-6. HTA is an abbreviation for Health Technology Assessment.

### Primary objective and outcomes

The primary objective is to assess the feasibility of integrated ultrasound surveillance for patients. The following feasibility outcomes at 12 months will be analysed:

Percentage attendance at ultrasound surveillance appointments.Percentage completion rates of components of ultrasound surveillance (ABPI, toe pressure and duplex).Percentage of participants undergoing reintervention for restenosis.

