### Secondary outcomes

The secondary objective is to provide pilot data for a subsequent trial of clinical effectiveness. For these purposes, secondary outcomes based on core reporting standards will be recorded. These will be measured at 13 months to allow for any reinterventions and their effects triggered from the 12-month visit to be captured. Secondary outcomes are:

Limb salvage (freedom from above-ankle amputation).Amputation-free survival.Reasons for major amputation.Serious reintervention complications (unplanned intervention, critical care admission or death).Major adverse cardiac or cerebrovascular events.Mortality and cause of death.

Questionnaire-based secondary outcomes will be self-reported by questionnaire at baseline, 1-month, 6-month and 12-month clinic visits.

Quality of life (European Quality of Life-five dimensions level (EQ-5D-L).Disease-specific quality of life (Vascular Quality of Life Questionnaire-6 (VASCUQOL-6)).Independence in activities of daily living (Barthel Index).Pain scores (Numeric Rating Scale-11 (NRS-11)).

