#### Intervention arm

Integrated standard clinical follow-up plus ultrasound surveillance at 1, 6 and 12 months with lower limb arterial Doppler scans performed in hospital, prior to specialist review. Scans will include ABPI, toe pressures and lower limb arterial duplex. It is anticipated that in future trials, one or more of these may be dropped.

Ultrasound results will be reported contemporaneously and those with a treated vessel restenosis of >50% or occlusion, a new inflow or outflow vessel stenosis of >50% or occlusion, an ankle pressure or toe pressure drop of ≥20 mm Hg or absolute pressure values for severe ischaemia (ABPI <0.4 or toe pressure <30 mm Hg)^8^ will be red flagged for clinician attention.

Antithrombotic therapy in both arms will be standardised to first line (aspirin 75 mg once daily and rivaroxaban 2.5 mg two times a day^9^) and second line (clopidogrel 75 mg once daily).^10^ If patients take full anticoagulation for another indication, this should continue, and initiation of additional antiplatelet therapy will be at the operator’s discretion. All patients will require therapy with either high-dose statin therapy (eg, atorvastatin 80 mg) or ezetimibe.^11^ All patients will be offered nicotine replacement therapy.

Reinterventions will be discussed in a local vascular multidisciplinary meeting considering patient wishes, fitness, complexity of procedure and concomitant factors which add to amputation risk (microvascular disease, deformity and infection).

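### The primary reintervention outcome is set at 12 months, the time of the last scan, so as worded it omits most reinterventions which that scan triggers

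*Protocol article*

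**What the plan says.** Under Primary objective and outcomes, three feasibility outcomes share one lead-in: "The following feasibility outcomes at 12 months will be analysed". They are attendance, completion of the scan components, and "Percentage of participants undergoing reintervention for restenosis".

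Under Intervention arm, the schedule is "Integrated standard clinical follow-up plus ultrasound surveillance at 1, 6 and 12 months". A red-flagged result does not lead straight to a procedure: "Reinterventions will be discussed in a local vascular multidisciplinary meeting".

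Under Secondary outcomes, the core clinical outcomes have a later time point, with the reason given: "These will be measured at 13 months to allow for any reinterventions and their effects triggered from the 12-month visit to be captured". That list holds limb salvage, amputation-free survival, reasons for major amputation, serious complications of reintervention, cardiac and cerebrovascular events, and death. A count of reinterventions is not on it. The questionnaire outcomes are not extended; they are "self-reported by questionnaire at baseline, 1-month, 6-month and 12-month clinic visits".

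Trial design gives the length of follow-up: "This trial will follow patients up for 13 months".

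**The concern.** The cut-off for the reintervention outcome coincides with the last scan. A procedure that follows from that scan needs a report, a multidisciplinary discussion and a date, so it will ordinarily take place after 12 months. The authors saw this and allowed an extra month, but attached it to outcomes that do not count reinterventions. The one outcome that does count them stays at 12 months.

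The Introduction names whether scans trigger treatment of restenosis as one of the uncertainties behind the study, and this is the only primary outcome that addresses it. Followed as written, it would reflect mainly the 1- and 6-month scans. There would also be an inconsistency in the report: a serious complication of a reintervention done between months 12 and 13 would count as a secondary outcome, while the reintervention itself would not count in the primary one.

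**Working it through.** **Time points side by side**

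| Item | Time point | Section |
|---|---|---|
| Attendance and component completion (primary) | 12 months | Primary objective and outcomes |
| Reintervention for restenosis (primary) | 12 months | Primary objective and outcomes |
| Third scan | 12 months | Intervention arm |
| Multidisciplinary discussion of reintervention | after the scan | Intervention arm |
| Core clinical secondary outcomes | 13 months | Secondary outcomes |
| Questionnaire outcomes | last at 12 months | Secondary outcomes |
| End of follow-up | 13 months | Trial design |

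Twelve months suits attendance and completion, because the last scan is then due. It does not suit reintervention, which comes after the scan. This mismatch follows from the text alone.

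**Illustration of size**

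Inputs from the article:
- Restenosis, from the Introduction: "Restenosis rates were reported at 33% after 1 year and 46% after 2 years".
- Reintervention, from the same paragraph: 10% at 1 year.
- Participants per arm, from Sample size: 35 randomised and about 30 analysed. The latter reproduces: 35 × 0.85 = 29.75.

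Assumptions, none of them given in the article:
- Restenosis accrues evenly, or at a constant hazard, up to 33% at 12 months.
- Restenosis that arises after the 6-month scan is found at the 12-month scan and not treated before it.
- A stated share of the restenoses found is treated.

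*Step 1: restenosis first detectable by scan at 12 months.*
- Even accrual: 0.33 × 6/12 = 0.165, which is 50% of first-year restenoses, or 0.165 × 35 = 5.8 participants.
- Constant hazard: cumulative restenosis at 6 months is 1 − (1 − 0.33)^(6/12) = 0.181. The remainder is 0.330 − 0.181 = 0.149, which is 45% of first-year restenoses, or 0.149 × 35 = 5.2 participants.

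*Step 2: reinterventions missed.* As one value for the treated share, take the ratio of the two cited one-year rates, 10/33 = 0.30.
- Even accrual: 0.165 × 10/33 = 0.050, or 5.0 points; 0.050 × 35 = 1.75 participants (1.5 of 30).
- Constant hazard: 0.149 × 10/33 = 0.045, or 4.5 points; 0.045 × 35 = 1.6 participants (1.4 of 30).

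*Step 3: other treated shares, constant hazard, ultrasound arm.*

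| Share treated | Counted to 13 months | Counted to 12 months | Difference | Missed of 35 |
|---|---|---|---|---|
| 25% | 0.330 × 0.25 = 8.3% | 0.181 × 0.25 = 4.5% | 3.7 points (0.149 × 0.25) | 1.3 |
| 50% | 0.330 × 0.50 = 16.5% | 0.181 × 0.50 = 9.1% | 7.4 points (0.149 × 0.50) | 2.6 |

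The 13-month column assumes that every treated case is treated within the extra month.

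**The case against.** **The phrase may be loose.** The 12-month time point is one lead-in over three outcomes. It may mean the 12-month programme and not a strict cut-off date. The full protocol and the study flow diagram are not shown and may define the window. This is fair as far as it goes: the text states no day on which counting stops, and with follow-up to 13 months the data need not be lost. But the article sets 12 and 13 months apart deliberately and gives the reason, and nothing in it carries the primary outcome past 12 months.

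**A reader might infer that the last scan can add no event at all.** The documents do not support that. A scan done slightly early, or a procedure arranged quickly, could still fall within 12 months. The supported statement is that most of that scan's yield would be omitted.

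**A reader might infer a biased treatment comparison.** The article says that the analysis is descriptive, and it specifies group differences only for the questionnaires. The control arm also has a specialist review at 12 months, with further imaging allowed if the limb deteriorates, so late reinterventions drop out there too. A larger loss in the ultrasound arm is plausible because of the extra trigger, but it cannot be quantified from the article.

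**The size is soft.** This stands. Some restenoses arising after month 6 will cause symptoms and be treated before the 12-month scan. The 10/33 ratio comes from published one-year rates, not from scan-detected disease. A reader might take the whole 15 to 16.5 points of late restenosis as the loss, but that supposes that every case is treated, whereas the multidisciplinary meeting weighs patient wishes, fitness and complexity. A shift of 5 points is also small beside the precision available: at 10% of 35, 1.96 × √(0.10 × 0.90 / 35) = 0.10, or about ±10 points. Still, this loss is systematic and avoidable, which sampling error is not.

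**Twelve months matches the only benchmark.** The cited 10% reintervention rate is a one-year figure. That is a real, small advantage of the present wording, and reporting both figures keeps it.

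**Conclusion.** The point holds. As worded, the primary reintervention outcome closes when the third scan is done. The extra month intended to capture the resulting reinterventions is attached only to the core clinical secondary outcomes, none of which counts them. The consequence is an understated descriptive rate in both arms, probably more so in the ultrasound arm.

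For illustration, about 45-50% of first-year restenoses would first be detectable by scan at 12 months. With about 30% treated, roughly 5 percentage points, or under 2 of 35 participants, would be missed. These figures rest on the assumed accrual pattern, on no earlier treatment of restenoses arising after month 6, and on the assumed treated share. The timing mismatch depends on none of them.

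No hypothesis test or sample size depends on this outcome. The article mentions progression criteria without stating them, so it cannot be shown that this rate decides whether a larger trial goes ahead. The wording should still be settled before analysis, because it defines a primary outcome.

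**What to change.** - Keep attendance and component completion at 12 months.
- Count reintervention for restenosis to 13 months in both arms.
- List separately, by arm, reinterventions agreed after the 12-month visit but not done by 13 months.
- Report the 12-month figure beside the 13-month one, so that the cited 10% one-year rate still has a like-for-like comparator.

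The cost is a sentence or two in the outcome definition and one extra line in a table. Follow-up already runs to 13 months, so no visits or participants are added and the sample size does not change. The one drawback is that the 13-month figure does not match the one-year benchmark exactly, which the paired 12-month figure covers.

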### Secondary outcomes

The secondary objective is to provide pilot data for a subsequent trial of clinical effectiveness. For these purposes, secondary outcomes based on core reporting standards will be recorded. These will be measured at 13 months to allow for any reinterventions and their effects triggered from the 12-month visit to be captured. Secondary outcomes are:

Limb salvage (freedom from above-ankle amputation).Amputation-free survival.Reasons for major amputation.Serious reintervention complications (unplanned intervention, critical care admission or death).Major adverse cardiac or cerebrovascular events.Mortality and cause of death.

Questionnaire-based secondary outcomes will be self-reported by questionnaire at baseline, 1-month, 6-month and 12-month clinic visits.

Quality of life (European Quality of Life-five dimensions level (EQ-5D-L).Disease-specific quality of life (Vascular Quality of Life Questionnaire-6 (VASCUQOL-6)).Independence in activities of daily living (Barthel Index).Pain scores (Numeric Rating Scale-11 (NRS-11)).

### Eligibility

The eligibility criteria are listed in table 1.

### Recruitment

Recruitment will be from three UK vascular units: Mid and South Essex, Imperial College Healthcare and Manchester University NHS Trusts. National Vascular Registry data show an average of six lower limb endovascular procedures per week in total across the three sites. We aim to recruit three participants per week, for a total of 70 over 6 months. Patients will receive a patient information sheet (PIS) during their endovascular procedure hospital stay. Patients will be allowed a further 1-week period to decide to take part. The consent process will be carried out according to the principles of good clinical practice, including a PIS and a signed informed consent form. A model consent form can be found in (online supplemental file 1). Following screening and consenting procedures, patients will undergo a series of baseline assessments or questionnaires to record demographic data and baseline patient-reported outcome measures.

To promote equality, diversity and inclusion, recruitment will be from three diverse sites, two in a multicultural, urban location and another in a semirural, predominantly Caucasian area, situated in the North, South and East of England. Interpreters will be provided for non-English speaking participants, and translation of materials will be provided on request. Travel costs have been incorporated to help overcome problems with transportation. As female patient recruitment has historically been challenging, a link to a female patient and public involvement team member and a female clinical vascular scientist has been made available. It will also be possible to provide participants with members of the research team from different ethnicities.

